## Abstract

**Introduction::**

Poor positioning of the child in relation to the breast and improper suckling are the main causes of nipple fissure. Treatment options for nipple fissures include drug therapy with antifungal and antibiotics, topical applications of lanolin, glycerin gel, creams and lotions, the milk itself, hot compresses, and silicone nipple shields. Studies involving light-emitting diode (LED) therapy have demonstrated anti-inflammatory properties, the enhancement of the wound repair process, and the control of pain. As it does not cause discomfort, is relatively inexpensive and may impede the discontinuation of breastfeeding, phototherapy could be a viable option for the treatment of nipple fissures.

**Aim::**

The principal objective of the proposed study is to evaluate the effectiveness of LED therapy for the treatment of nipple fissures in postpartum mothers.

**Materials and methods::**

One hundred patients treated with a medical diagnosis of bilateral nipple trauma classified as nipple fissures or cracks will participate in the study, randomized into 2 groups: The control group will receive orientation regarding breast care and adequate breastfeeding techniques. The experimental group will receive the same orientation and phototherapy sessions using a device developed especially for the treatment of nipple trauma. Both groups will be followed up for 6 consecutive weeks.

## Introduction

1

During pregnancy and in the postpartum period, care is fundamental to minimizing problems, such as nipple trauma^[1]^ due to the occurrence of fissures associated with an inflammatory process of the upper layer of the dermis.^[2]^ Around 98% of women can physiologically breastfeed, but many mothers avoid this practice. Nipple fissures are the second major cause of the discontinuation of breastfeeding, followed by the sensation of insufficient milk that many mothers have, leading to the habit of bottle feeding.^[3]^ Nipple fissures are classified as either circular or longitudinal and vary in size. A circular fissure is commonly located at the nipple-areolar junction, whereas a longitudinal fissure is situated throughout the entire length of the nipple either vertically or horizontally, dividing it into 2 halves.^[4]^

Nipple fissures tend to appear in the second or third week of the postpartum period and are a frequent cause of pain that often leads to premature discontinuation of breastfeeding.^[2]^ Poor positioning of the child in relation to the breast, an inadequate frequency or duration of breastfeeding, and improper suckling are the main causes of nipple fissure.^[1]^ Since 1991, both the World Health Organization (WHO) and the United Nations Children's Fund (UNICEF) have dedicated international efforts to protecting, promoting, and supporting exclusive breastfeeding until an infant reaches 6 months of age.^[5]^

The discontinuation of breastfeeding deprives an infant of the essential nutrients, growth factors, and important immunological components in breast milk. For the mother, not breastfeeding hinders uterine involution, increases the risk of postpartum hemorrhage, and increases the risk of ovarian and breast cancer, not to mention the affective aspect of the mother–child bond that is created through the breastfeeding experience.^[6]^

Treatment options for nipple fissures include drug therapy with antifungal agents and antibiotics, topical applications of lanolin, glycerin gel, creams and lotions, the milk itself, hot compresses, silicone nipple shields, and phototherapy.^[7,8]^ It should be stressed that nipple fissures can be a gateway for bacteria, which could lead to more serious conditions, such as abscess and mastitis.^[9,10]^

Phototherapy is the use of electromagnetic waves within the red and infrared spectra that are applied to biological tissues with the aid of low-level light devices, such as light amplification by stimulated emission of radiation (laser) and a light-emitting diode (LED). Studies have demonstrated the anti-inflammatory properties of phototherapy, with the enhancement of the wound repair process^[11–13]^ and the control of pain.^[14,15]^ As it does not cause discomfort, is relatively inexpensive, and may impede the discontinuation of breastfeeding, phototherapy could be a viable option for the treatment of nipple fissures.^[16]^

## Methods/Design

2

The principal objective of the proposed study is to evaluate the effectiveness of LED therapy for the treatment of nipple fissures in postpartum mothers. The secondary objectives are to evaluate the effect of LED therapy on the healing of nipple fissures in postpartum mothers; evaluate the effect of LED therapy on the control of pain during breastfeeding in postpartum mothers with nipple fissures; and evaluate the impact of the treatment of nipple fissures with LED therapy on the quality of life of postpartum mothers.

This protocol follows the SPIRIT (Standard Protocol Items for Randomized Trials) recommendations displayed in Fig. 1 and Table 1 .

**Figure 1 F1:**
[figure not shown]
Schedule of enrolment, interventions, and assessments of the study.

**Table 1 T1:**
[figure not shown]
SPIRIT 2013 checklist: recommended items to address in a clinical trial protocol and related documents^∗^.

**Table 1 (Continued) T2:**
[figure not shown]
SPIRIT 2013 checklist: recommended items to address in a clinical trial protocol and related documents^∗^.

### Methods

2.1

A controlled clinical trial will be conducted to evaluate the effects of LED therapy on tissue healing, pain, and quality of life in postpartum mothers with nipple fissures. One hundred patients treated at the Mandaqui Hospital in the city of São Paulo, Brazil, with a medical diagnosis of bilateral nipple trauma classified as nipple fissures or cracks will participate in the study. All patients must sign an informed consent form.

All participants will answer a questionnaire addressing basis information (age, gestation time, and infant's age) and history of nipple fissures, will indicate their pain at baseline using the Visual Analog Scale (VAS), and will answer a quality-of-life questionnaire. All participants will sign a statement of informed consent before the onset of the study.

### Eligibility criteria

2.2

The following will be the inclusion criteria:(1)Nursing mothers aged 18 years or older;(2)Diagnosis of nipple fissure and nipple pain with a minimum score of 1 on the Store and Champion scales;(3)Having given birth to a healthy, full-term child;(4)Performing exclusive breastfeeding;(5)Newborn with no oral, palatal or maxillofacial abnormalities;(6)Newborn weighing between 2500 and 4000 g.

The following will be the exclusion criteria:(1)History of psychological disorder;(2)Presence of mastitis;(3)Bacterial or fungal infection in breasts;(4)Use of breast pump or plastic nipple.

The participants will be randomly allocated to either the experimental or control group using a randomization site (http://www.randomization.com). The control group will receive orientation regarding breast care and adequate breastfeeding techniques. The experimental group will receive the same orientation and phototherapy sessions using a device developed especially for the treatment of nipple trauma. Both groups will be followed up for 6 consecutive weeks. The information will be registered in an Excel Program.

The patients will be submitted to an initial evaluation by an examiner blinded to the group allocation. The aim of the evaluation will be to characterize the participant (age, skin color, number of children, schooling, type of birth, previous breastfeeding experience, and time of puerperium) and the nipple [color and type (protruded, semi-protruded, inverted, or hypertrophic)]. After the evaluation, the participants will be sent to begin the interventions.

The patient will be instructed not to use creams, soaps, or any type of ointment on the nipples, to wear bras with wide, firm straps to support the breasts, to remain in a comfortable position during breastfeeding with the infant's body turned completely toward the mother. Secure the breast in a C shape to facilitate the infant's latching, wait for the infant to empty the first breast offered completely before moving to the other breast, and place the tip of the little finger in the corner of the infant's mouth to facilitate its removal from the breast. This information will be given to the women at the initial evaluation as well as in the third and sixth weeks always by the same researcher in both oral and printed (educational brochure) form.^[16]^

The strategy to adherence to the intervention protocol will be information about nipple fissures and complications. All participants, regardless of group, will be part of a support group for the mother and baby with educational activities and care.

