### Statistical analysis

2.7

The statistical analysis will be performed with the aid of SPSS 20.0 (IBM Corporation, Armonk, NY). The Kolmogorov–Smirnov test will be used to determine the normality of the data. Depending on the distribution, the data will be expressed as mean and standard deviation for continuous variables. Repeated-measures analysis will be performed considering group and evaluation time. The Mann–Whitney test, *t* test for independent samples, and Fisher exact test will be used for the comparisons, and a *P* value < .05 will be considered indicative of statistical significance. The statistical analysis will be blinded.

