## Discussion

3

This article describes the protocol for a randomized, controlled, clinical trial for the evaluation of the effect of LED therapy for the treatment of nipple fissures in nursing mothers. One of the advantages of the study is the action of LED therapy in the control of nipple pain and the induction of healing of the traumatized breast tissue.^[16]^

Nipple fissures and pain can occur during the lactation period, especially in the initial days of breastfeeding and can even lead to premature weaning. Breast milk is nutritionally ideal for the healthy development of a child and breastfeeding is ideal for orofacial growth and development.^[8,13]^

Nipple pain is generally reported 3 to 6 days after giving birth and can persist for up to 6 weeks.^[1]^ Untreated fissures can compromise the infant's nutrition and can lead to complications, such as mastitis, bleeding, infection, and abscess.^[19]^ The treatments described in the literature include medications, natural extracts, compresses, and lanolin. However, these treatments are not effective with regard to both tissue healing and the control of pain.

Considering the importance of breastfeeding and the high prevalence of nipple fissures, this study proposes a novel way to control nipple pain and accelerate the healing process of nipple fissures through the use of LED therapy, which is a noninvasive technique with no side effects, such as the allergic reactions that can be caused by the ingestion of substances.

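### Time since birth is recorded and plausibly prognostic for pain, but the article describes no use of it in allocation or analysis; stratifying and adjusting would gain precision and guard against chance imbalance

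*Protocol article*

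**What the plan says.** All references are to the protocol article.

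- **Entry.** Eligibility criteria (2.2) lists six inclusion criteria, beginning "1)Nursing mothers aged 18 years or older;(2)Diagnosis of nipple fissure and nipple pain with a minimum score of 1 on the Store and Champion scales" and ending "6)Newborn weighing between 2500 and 4000 g". The four exclusions are "1)History of psychological disorder;(2)Presence of mastitis;(3)Bacterial or fungal infection in breasts;(4)Use of breast pump or plastic nipple". None is expressed in days since birth or in age of the fissure.
- **Allocation.** The same section says that women are allocated at random through a randomisation website. It mentions no strata. Sample size (2.6) gives 50 per group.
- **Follow-up.** "Both groups will be followed up for 6 consecutive weeks", counted from entry.
- **Natural course.** The Discussion states: "Nipple pain is generally reported 3 to 6 days after giving birth and can persist for up to 6 weeks". The Introduction states: "Nipple fissures tend to appear in the second or third week of the postpartum period".
- **Data collected.** The baseline evaluation records "schooling, type of birth, previous breastfeeding experience, and time of puerperium", and Methods (2.1) adds the infant's age.
- **Analysis.** Statistical analysis (2.7) states: "Repeated-measures analysis will be performed considering group and evaluation time". No baseline covariate is named.

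**The concern.** By the protocol's own account, pain begins within days of birth and does not last indefinitely. Two women with the same pain score at entry, one in the first postpartum week and one several weeks later, may have different expected courses over the next 6 weeks whichever arm they are in. That is what makes a baseline variable prognostic.

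If the variable is used in neither allocation nor analysis, two things follow. The variation it explains stays in the error term, so the treatment comparison is less precise than it could be. And in any one trial of 50 per arm, the arms can differ by chance in how long after birth women entered, with nothing described to correct the resulting shift. Reduction of nipple pain is one of the main outcomes (Outcomes, 2.5), so the principal comparison is affected.

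**Working it through.** **1. Is the protocol's sample size reproducible?** No. Sample size (2.6) gives 80% power, α = 0.05, dropout of 10% to 15% and 50 per group, but no effect size, standard deviation or event rate. Solving backwards (two-sided α assumed, normal approximation), the detectable standardised difference is (1.960 + 0.842) × √(2/n):

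- n = 50: 2.802 × √(2/50) = 0.56
- n = 45 (10% dropout): 0.59
- n = 42.5 (15% dropout): 0.61

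These figures serve only as a yardstick below.

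**2. Chance imbalance.** Let p be the share of women who enter late. The documents do not give p, so it is varied. With 50 per arm and no stratification, the standard error of the between-arm difference in that share is √(2p(1−p)/50). The chance of a difference of 10 points or more is P(|Z| ≥ 0.10/SE).

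| Assumed p | SE | 10 points or more | 20 points or more |
|---|---|---|---|
| 0.10 | 0.060 | 10% | 0.1% |
| 0.20 | 0.080 | 21% | 1% |
| 0.50 | 0.100 | 32% | 5% |

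The row p = 0.50 gives the largest standard error. If the Introduction is right that fissures tend to appear in week 2 or 3, the smaller shares may be more realistic for a cut placed well after that.

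**3. What an imbalance does.** If late and early entrants differ in expected outcome by δ standard deviations regardless of treatment, an imbalance of 10 points shifts the unadjusted difference by 0.10 × δ. For δ = 0.5 that is 0.05 SD, or 0.05/0.56 = 9% of the detectable difference. For δ = 1 it is 0.10 SD, or 18%. The shift can favour either arm and averages zero over randomisations. δ is assumed.

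**4. Precision left unused.** If time since birth has correlation ρ with the outcome, adjustment multiplies the residual variance by 1 − ρ². A comparison with 80% power unadjusted then has power Φ(2.802/√(1−ρ²) − 1.960).

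| Assumed ρ | Variance removed | Power |
|---|---|---|
| 0.1 | 1% | 80% |
| 0.3 | 9% | 84% |
| 0.5 | 25% | 90% |

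If the baseline value of the outcome is also in the model, ρ is the partial correlation given that value, and the added gain from time since birth may be smaller.

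**5. The dilution scenario, as a worst case.** Suppose a share f of women contribute no treatment contrast at all and the SD is unchanged. The effect becomes (1−f) times its size, and power is Φ(2.802(1−f) − 1.960):

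- f = 10%: Φ(0.562) = 71%
- f = 20%: Φ(0.281) = 61%
- f = 30%: Φ(0.001) = 50%

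The sample size cancels, so these values hold for any evaluable n that gives 80% power at f = 0. Neither f nor the assumption of zero contrast comes from the documents.

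**The case against.** A reader might infer something stronger: that women close to natural recovery can be enrolled, that they dilute the effect, and that an entry window is needed. The documents do not carry that.

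- The 6-week figure is a maximum and concerns pain. It can be read as duration from onset or as time since birth, so it does not show that a woman entering in week 5 has one week of pain left.
- No natural healing time is given for fissures, only their time of onset. A woman who still has fissures and pain in week 5 may be a slow healer with more to gain.
- Zero contrast in late entrants is extreme. Fissures are measured at sessions 1 and 3 and pain at sessions 1 and 4, at three sessions a week, so faster improvement would show about a week after entry.
- The word used for the infant in criteria 5 and 6 suggests some limit on age, although it is not defined in days.
- An entry window would not keep follow-up inside 6 weeks from birth: entry on day 5 ends near day 47 (5 + 42), and entry on day 21 near day 63 (21 + 42).

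All of this stands. It is also fair that chance imbalance can arise in any unstratified baseline variable, that randomisation balances it on average, and that covariates are often left to an analysis plan, which is not shown here. What remains is that the protocol's own description singles this variable out as related to the course of pain, that the trial already collects it, and that strata can be set only before allocation, so an analysis plan cannot add them afterwards.

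**Conclusion.** The point holds as an inexpensive improvement to the design and analysis, not as an error that threatens validity. Time since birth is a plausible prognostic factor for pain on the protocol's account; for fissure healing the documents are silent. Its absence from the described allocation and model is a matter of precision and chance imbalance, not of systematic bias between arms.

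The size depends on quantities the documents do not give. With a late share of 10% to 50%, an imbalance of 10 points or more occurs in about 10% to 32% of trials. With a correlation of 0.1 to 0.5, adjustment removes 1% to 25% of the variance. The power figures of 71%, 61% and 50% are illustrative worst cases and should not be quoted as the expected loss. Entry at any time since birth is a legitimate choice, and an upper limit is optional.

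**What to change.** 1. **If randomisation has not started:** stratify the list by time since birth, for example up to 14 days versus later, with blocks within each stratum so that the stratification takes effect. The cut is an example; the sponsor may choose another.
2. **In either case:** name time since birth, together with the baseline value of the outcome, as covariates in the repeated-measures model for pain and fissure size. If allocation has begun, do this alone, and fix it before the data are unblinded.
3. **Wording:** state whether the weight range in criterion 6 means birth weight or weight at enrolment. The first sets no limit on time since birth; the second would act as an age limit that varies with birth size.

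The cost is two randomisation lists instead of one and one sentence in the analysis section. The variable is already collected and no woman is lost to enrolment. A fixed entry window remains the sponsor's choice; it would lose some late presenters.

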### Ethical aspects

2.3

This study received approval from the human research ethics committee (certificate number: 2.540.438) and is registered with ClinicalTrials (number: NCT03496753).

### Intervention

2.4

#### Phototherapy - LED

2.4.1

The following will be the phototherapeutic parameters: total spot area: 1.44 cm^2^; continuous emission mode; output power: 10 mW; infrared wavelength (880–904 nm); fluence: 4 J/cm^2^; and application time: 10 minutes/session. Sessions will be held 3 times a week on alternating days for 6 consecutive weeks, totaling 18 sessions.

#### Clinical parameters for evaluation of fissures

2.4.2

Nipple fissures will be measured in the first, third, sixth, ninth, 12th, 15th, and 18th sessions using digital calipers (Black Bull) and classified at the beginning and end of the study based on Pereira et al ^[17]^: small (≤ 3 mm), medium (> 3 and ≤ 6 mm), or large (> 6 mm).

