### Outcomes

2.5

The main outcomes of the study will be the treatment of nipple fissures and a reduction in nipple pain. The secondary outcomes will be related to the quality of life of the participants.

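### The protocol sets out to speed up fissure healing, but its listed analyses do not use the healing time that the scheduled caliper sessions already provide

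*Protocol article*

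**What the plan says.** All references are to the protocol article.

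- **Aim.** Section 3 (Discussion) says that the study offers a way to "control nipple pain and accelerate the healing process of nipple fissures". The secondary objective in section 2 is worded more generally: "evaluate the effect of LED therapy on the healing of nipple fissures in postpartum mothers".
- **Outcome.** Section 2.5: "The main outcomes of the study will be the treatment of nipple fissures and a reduction in nipple pain". No fissure variable or time point is attached.
- **Measurement.** Section 2.4.2: "Nipple fissures will be measured in the first, third, sixth, ninth, 12th, 15th, and 18th sessions using digital calipers". The fissures are also "classified at the beginning and end of the study" as small (up to 3 mm), medium (over 3 and up to 6 mm) or large (over 6 mm).
- **Follow-up.** Section 2.2: "Both groups will be followed up for 6 consecutive weeks".
- **Analysis.** Section 2.7 lists a repeated-measures analysis by group and evaluation time, and Mann–Whitney, t and Fisher exact tests. It does not say which test serves which outcome, mentions no adjustment for baseline size, and names no time-to-healing method.

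**The concern.** Hastening is a question about when fissures close. The class cannot answer it well. It is read only at the two ends of follow-up, and a closed fissure has no level of its own, so it cannot be told apart from an open one of 3 mm or less. If most fissures in both arms close well before the last session, a comparison at that session shows little even when one arm healed much sooner.

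The repeated-measures analysis of caliper size does use the intermediate sessions, but as worded it carries two costs. Differences between women in starting size remain in the error term. Sessions after closure add zeros in both arms and dilute the average difference. A real shortening of healing time could then be reported as no effect, although the readings that would show it had been taken.

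**Working it through.** **The plan's own figure.** Section 2.6 gives 50 women per group for 80% power at α = 0.05, with 10% to 15% dropout. It states no effect size, SD or healing rate, so the 50 cannot be reproduced. With 15% loss, 50 × 0.85 = 42.5, taken as 43 evaluable per arm. The detectable standardised difference (two-sided) is (1.960 + 0.842) × √(2/43) = 0.60. That is plausible, but it says nothing about healing time.

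**Session days.** Three sessions a week on alternating days (section 2.4.1), taken as Monday, Wednesday and Friday, put caliper sessions 1, 3, 6, 9, 12, 15 and 18 on days 0, 4, 11, 18, 25, 32 and 39. After the first interval the spacing is 7 days, so closure is known to within about a week.

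**Assumptions (not document figures).** Healing times are exponential. LED halves healing time (hazard ratio 2). Control medians run from 10 to 42 days. Baseline size is 5 mm (SD 2), shrinking linearly to closure. Both arms are measured on the same days.

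**Healed by the last session.** Control: 1 − 0.5^(39/m), with m the control median in days. LED: 1 − 0.5^(78/m). For m = 14, control is 1 − 0.5^2.79 = 85.5% and LED is 1 − 0.5^5.57 = 97.9%.

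**Power by simulation (1,000 runs per row, 43 per arm, two-sided 0.05).** Log-rank uses healing times as read at the caliper sessions. The repeated-measures columns use all seven readings without adjustment, with the Greenhouse–Geisser correction for the interaction. Adjusted mean size is the average of the six post-baseline readings, with baseline size as covariate.

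| Control median (days) | Healed by day 39, control / LED | Log-rank | Repeated measures: group | Repeated measures: interaction | Adjusted mean size | Fisher, healed at end |
|---|---|---|---|---|---|---|
| 10 | 93% / 100% | 85% | 59% | 54% | 81% | 6% |
| 14 | 86% / 98% | 84% | 62% | 50% | 80% | 37% |
| 21 | 72% / 92% | 84% | 67% | 46% | 82% | 60% |
| 28 | 62% / 86% | 78% | 63% | 42% | 78% | 66% |
| 42 | 48% / 72% | 67% | 55% | 46% | 73% | 57% |

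**Sensitivity to the assumed curve and effect.**

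- Exponential healing, 1.5-fold shortening, same medians: log-rank 26–43%, group effect 23–28%, interaction 16–22%, adjusted mean size 30–40%. No method is well powered here.
- Weibull healing with shape 1.5, 1.5-fold: log-rank 57–75%, group effect 37–46%, interaction 27–41%, adjusted mean size 62–71%.
- Weibull healing with shape 1.5, 2-fold: log-rank 97–100%, group effect 74–86%, interaction 70–87%, adjusted mean size 98–99%.
- Another set of assumed curves, over the same medians and 1.5- to 2-fold shortening, gave about 46–98% for log-rank, 25–82% for the group effect and 22–80% for the interaction.

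The limits move with the curve, but log-rank is ahead of both unadjusted repeated-measures tests throughout. Its lead over the group effect is smallest (26% against 23%) at a 42-day median with exponential healing and a 1.5-fold effect. The end-of-study healed comparison is close to zero when nearly all fissures have closed by then: 6% or less at a 10-day median in every case above.

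**The case against.** Four points can be made for the plan, and each has some force.

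**The plan does not rest on the end of follow-up.** A reader might infer that speed is judged only at week 6, and set an end-of-study Fisher power of 6% against 85% for log-rank. The documents do not support this. Only the size class is confined to start and end. Caliper size is measured seven times and a repeated-measures analysis is planned. Fisher's test is listed without an outcome, and healed at session 18 is not a variable that the protocol defines. The fair comparator is the repeated-measures analysis, against which the loss is real but much smaller.

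**The 6-week figure is not about fissures.** A reader might also infer that, by the protocol's own account, the condition will have resolved in both groups by the end. The sentence reads "Nipple pain is generally reported 3 to 6 days after giving birth and can persist for up to 6 weeks". It concerns pain, and it is an upper limit. Section 1 says only that fissures tend to appear in the second or third postpartum week. How fast they close is therefore an assumption.

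**Log-rank is not uniquely right.** Size over time is a legitimate measure of healing, and a group-by-time difference reflects speed. Adjusted mean size is close to log-rank and passes it at a 42-day median under exponential healing (73% against 67%). With long control medians, a Mann–Whitney test on final size can also match log-rank. It cannot be said that log-rank wins in every setting.

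**Wording and detail.** The proposal to "accelerate the healing process of nipple fissures through the use of LED therapy" stands in the Discussion, not in the objectives, and an article may leave model detail to a fuller document. That is a reason for modest weight. It does not remove the point, because sections 2.4.2 and 2.7 do fix when the class is read and which analyses are listed.

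No error is shown for pain. It is recorded on the VAS at six sessions (section 2.4.3) and is open to the same repeated-measures analysis.

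**Conclusion.** The point holds as a mismatch between a stated aim and the listed analyses. The protocol wants to show faster healing, its fissure class has no closed level and is read only twice, and nothing listed uses the healing time that the caliper schedule gives.

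The size is conditional. With two-fold shortening and exponential healing, log-rank gains about 12 to 26 percentage points over the planned unadjusted group effect (67 − 55 at a 42-day median, 85 − 59 at 10 days). A week-6 healed comparison would fail almost completely only if fissures close early. Much of the gain over the planned analysis can also be had by adjusting caliper size for baseline. All of this rests on assumed healing curves, a linear shrinkage model and 43 evaluable women per arm. Weight: minor to moderate, as a cheap improvement.

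**What to change.** 1. Define healed as no open fissure on either nipple at a scheduled caliper session, and date it to the first such session.
2. Name time to healing as the fissure comparison. Analyse it as grouped or interval-censored data, by log-rank or a complementary log-log model, adjusted in the model for baseline fissure size and time since birth. Both are already recorded (sections 2.4.2 and 2.2). Report median healing times and a hazard ratio with 95% CI.
3. Keep caliper size over the sessions, adjusted for baseline size, as the supporting analysis.
4. Keep the week-6 size class as descriptive.

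The cost is wording only, with no added visits, measurements or participants, provided both arms are measured on the same schedule. There are two drawbacks. Healing is known only to the interval between sessions, which the grouped or interval-censored model handles. Partial shrinkage does not count as healing, which the supporting size analysis covers.

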### Sample size

2.6

The sample size was calculated based on the results of previous studies^[18]^ and considering a possible dropout rate of 10% to 15% throughout the follow-up period. For a 95% confidence interval, 80% test power, and α = 0.05, it was determined that 50 women would be needed for each group (total: 100 participants).

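### The end-of-study fissure size classes have no class for a closed fissure, so that classification cannot show complete healing

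*Protocol article*

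**What the plan says.** Section 2.4.2 of the protocol article describes two fissure assessments. The first is a length: "Nipple fissures will be measured in the first, third, sixth, ninth, 12th, 15th, and 18th sessions using digital calipers". The second is a size class. Fissures are "classified at the beginning and end of the study" as "small (≤ 3 mm), medium (> 3 and ≤ 6 mm), or large (> 6 mm".

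Healing matters to this trial. Section 2 lists as an objective to "evaluate the effect of LED therapy on the healing of nipple fissures in postpartum mothers", and section 2.5 states: "The main outcomes of the study will be the treatment of nipple fissures and a reduction in nipple pain". No section defines when a fissure counts as healed, or says how a nipple with no remaining fissure is to be classified.

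On analysis, section 2.7 plans a repeated-measures analysis by group and time. It then names the Mann–Whitney test, the *t* test and Fisher's exact test for comparisons, without tying any of them to a particular variable.

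**The concern.** The three classes suit baseline. Section 2.2 requires "Diagnosis of nipple fissure and nipple pain with a minimum score of 1 on the Store and Champion scales", so every woman has a fissure to classify at entry. The same classes are then reused at the end of the study, when the result hoped for is that no fissure remains. The scale has no place for that result.

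At stake is the meaning of the end-of-study table. If closed nipples are coded as small, cure and partial shrinkage are merged, and women who entered with a small fissure show no change however well they do. If closed nipples are left unclassified, the successes drop out of the table. In both cases the rule for what counts as healed would have to be made up later, possibly with the data in view.

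**Working it through.** **Step 1. Apply the written limits** (section 2.4.2) to test lengths:

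| Length (mm) | Class as written |
|---|---|
| 0 | small |
| 0.1 | small |
| 3 | small |
| 3.1 | medium |
| 6 | medium |
| 6.1 | large |

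0 mm and 3 mm share a class. A fissure going from 2 mm to 0 mm reads small to small, so no change is recorded. A fissure going from 7 mm to an open 3 mm reads large to small, the same end class as a cure. Shrinkage from large to medium to small is still visible. Closure is not, nor is any gain in a fissure that starts small.

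**Step 2. The plan's own figure.** The only computed figure is 50 women per group, from "For a 95% confidence interval, 80% test power, and α = 0.05". Section 2.6 gives no effect size, standard deviation or rate, so it cannot be reproduced. The point does not depend on it. It is used only to set an evaluable number: with 15% dropout, the upper end of the stated range, 50 × 0.85 = 42.5, taken as 43 per group.

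**Step 3. What a small-versus-larger split would lose.** The article gives no healing rates, so these are assumptions: 50% against 80% healed, or 60% against 85%, with a share *s* of unhealed women still above 3 mm. Then

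P(small) = 1 − (1 − P(healed)) × *s*.

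For example, with *s* = 20%, 1 − 0.50 × 0.20 = 90% and 1 − 0.20 × 0.20 = 96%. Power is that of the two-sided Fisher test at 0.05, found by summing the binomial probabilities of every pair of counts (43 per group) that the test rejects.

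| Assumed healed | *s* | P(small) by group | Power, small v larger | Power, healed yes/no |
|---|---|---|---|---|
| 50% v 80% | 20% | 90.0% v 96.0% | 7% | 80% |
| 50% v 80% | one third | 83.3% v 93.3% | 20% | 80% |
| 50% v 80% | 50% | 75.0% v 90.0% | 34% | 80% |
| 60% v 85% | 20% | 92.0% v 97.0% | 4% | 68% |
| 60% v 85% | one third | 86.7% v 95.0% | 14% | 68% |
| 60% v 85% | 50% | 80.0% v 92.5% | 29% | 68% |

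In the limit *s* = 0, everyone ends as small in both groups and the contrast vanishes.

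**Step 4. What the caliper length keeps.** Take the same assumptions, record a closed fissure as 0 mm, and add one more: open lengths are uniform on 0.2 to 3 mm or on 3 to 7 mm. A simulated Mann–Whitney test on final length then has about 81% to 83% power for 50% against 80% healed, and about 74% for 60% against 85%. That is no worse than healed yes/no (80% and 68%). The loss in step 3 therefore belongs to the classes, not to the trial's fissure data.

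**The case against.** The strongest reply is that the classes are only a size descriptor. The healing evidence would come from seven caliper readings, for which section 2.7 offers a repeated-measures analysis and a Mann–Whitney test. This stands. Step 4 shows that, on the assumed rates, the length loses nothing against a healed yes/no outcome. A reader might infer that the trial cannot detect a difference in complete healing. The article does not support that, because a closed fissure can be recorded as 0 mm at the 18th session.

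A reader might also infer that Fisher's test, which ignores order, is the planned test for these classes. The article says only "Fisher exact test will be used for the comparisons", alongside two other tests, and assigns none of them. Fisher's test could serve baseline descriptors such as nipple type or type of birth, and Mann–Whitney could serve the ordered classes. Nor does section 2.5 say that the classes are the main outcome.

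Finally, one may say that a size class applies only to a fissure that is present, so a closed nipple has nothing to classify. That is a natural reading, but the article does not state it, and it does not close the gap: healed nipples would then fall in no class, with no rule for reporting them. A full protocol might supply such a rule. Even so, the class limits and their use at the end of the study are fixed in the article, and as written they do not work there.

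**Conclusion.** The point holds for the categorical end-of-study classification and for nothing wider. As written, that classification either merges a healed nipple with an open fissure of up to 3 mm or leaves it unclassified, and a fissure that starts small cannot register improvement. This follows from the class limits alone and needs no assumption.

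The size of the loss is uncertain. The drop to 4% to 34% power, against 68% to 80% for healed yes/no, rests on assumed healing rates and an assumed share of larger residual fissures, and it applies only to a two-way split of small against larger. The article gives neither the baseline size distribution nor healing rates. Because the serial lengths remain available, the severity is moderate. The correction costs almost nothing and makes the end-of-study table answer the healing objective, so it should be made.

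**What to change.** In section 2.4.2, add an end-of-study class *healed (no open fissure, 0 mm)* and define small as > 0 and ≤ 3 mm, leaving medium and large as they are. Report complete healing as yes/no per woman from the caliper reading at session 18. Since section 2.1 enrols women with bilateral trauma, state that yes means no open fissure on either nipple.

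In section 2.7, state that the four ordered classes are compared with the Mann–Whitney test already listed, and healed yes/no with Fisher's exact test.

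The cost is one line in each section. The 0 mm value comes from readings already planned, so no visit, measurement or change in sample size is needed. The wording should be settled before group assignments are revealed to the analyst, so that the meaning of healed is not chosen after the results are seen.
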